**Figure 1 F1:**
[figure not shown]
**CONSORT flowchart of trial design**.

### Setting

This is a single-centre trial based in NHS Forth Valley, Scotland.

### Ethical Approval

Ethical approval has been obtained from Fife and Forth Valley Research Ethics Committee (REC ref. no. 08/S0501/6).

### Intervention

Participants in the intervention group will receive 9 visits from the researcher in their own home, including 4 visits to complete questionnaires, 2 one hour intervention sessions, and 3 other visits to drop off or pick up pedometers.

#### Session 1

The researcher will elicit any maladaptive beliefs the participant has about their illness, or about walking. Information will be provided about the consequences of the illness, and about the behaviour-health link in order to modify illness and walking beliefs. Motivational interviewing techniques will be used to deliver the intervention, asking open questions, prompting the participant to make self-motivating statements and evaluations of their own walking behaviour and aiming to move participants to a point where they have expressed motivation or intention to change their walking behaviour. A copy of the schedule used to guide the discussion in Session1 is provided in Additional File 1.

#### Session 2

The researcher will work with the participant to draw up an individualised walking action plan, based on the recommendation of walking to near maximal pain three times a week [8]. Participants will be encouraged to think about how they can adapt their daily routines to incorporate a half hour of continuous walking, and will also be encouraged to think of possible barriers which may prevent them from following their action plan, and strategies to cope with these barriers. Sniehotta et al [19] found that a combination of action planning and coping planning led to much greater improvement in physical exercise than action planning alone. Action plans will then be typed up and laminated, and posted out to participants. A copy of the template for an action plan is provided in Additional File 2.

### Control

Participants in the control group will receive 8 visits from the researcher, in their own home, including 4 visits to complete questionnaires and a further 4 visits to either drop off or pick up the pedometer. This is only 1 less visit from the researcher than participants in the intervention group. The researcher will engage control group participants in non-walking related conversation in an attempt to control for the potentially confounding effects of social contact.

### Usual Care

Participants in the intervention group and control condition will receive usual care while participating in the study. All participants will be diagnosed as having intermittent claudication by the Vascular Assessment Nurse, who provides all patients with an information sheet about Peripheral Arterial Disease and advises patients to 'stop smoking and start walking'. All participants then attend an outpatient clinic to meet with a Vascular Surgeon, who will discuss appropriate treatment with the patient. Appropriate treatment depends on the age and health of the patient, the size and location of the narrowing of the artery, and on the patient's wishes. If the patient chooses surgical intervention they will then be put on a waiting list for surgery or angioplasty. Approximately 56% of patients diagnosed with IC in NHS Forth Valley proceed to receive angioplasty or surgery, usually within 6 months of diagnosis. If the patient chooses conservative treatment, they will be invited to attend a further outpatient clinic in 3 months time, and then discharged if their claudication symptoms remain stable. Patients who receive angioplasty are followed up by the surgeon for 1 year and then discharged; patients who receive surgery are followed up by the surgeon for 5 years.

At the time of 4 month follow-up in the RCT, all patients will have attended the outpatient clinic to meet the Vascular Surgeon, and a treatment decision will have been made. However, patients will be on a waiting list and will not have received treatment.

### Telephone Calls

The researcher will call participants in both groups, 6 and 12 weeks after recruitment into the study. The purpose of the call will be to:

• Intervention group - discuss progress against the action plan with participants in the intervention group, playing particular attention to barriers to walking, and encouraging participants to use their coping plans, and come up with alternative strategies to overcome barriers. Changes to a participant's action plan or coping plan may be agreed with a participant in the phone call.

• Both groups - ask participants if they have heard from the hospital and what treatment, if any, has been agreed upon.

• Both groups - ask participants to answer 5 standard questions about general health, satisfaction with health, quality of life [20], pain rating [21], and pain free walking distance [22].

### Outcome Measures

Measures will be taken for participants in both arms of the study, at baseline, 4 months, 1 and 2 year follow-ups. All questionnaires will be administered by the researcher.

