### Other Measures

Self-reported walking ability will be measured with the question 'How far can you walk, aided or unaided, under normal circumstances before the onset of pain?' to which there are 6 possible responses - '0 yards', 'up to 100 yards', 'up to 250 yards', 'up to half a mile', 'up to 1 mile', 'more than a mile'. The question is adapted from Mondillo et al's [22] Claudication Self-Assessment with the distances being re-formatted from metres to yards to reflect the fact that older patients are more likely to be confident measuring distance in imperial units. In order to measure frequency of walking to the onset of pain, participants are asked 'In general, how frequently do you walk that distance?' with 6 possible responses - 'never', 'once or twice a month', 'once a week', '2-3 times a week', '4-5 times a week', and 'everyday'.

A self-report measure of walking will also be completed, as a comparison for walking as measured by pedometer. The International Physical Activity Questionnaire (IPAQ) [23] is a self-report measure of physical activity with 4 items measuring time spent in vigorous and moderate activity, time spent walking, and time spent sitting.

Quality of life will be measured using the Intermittent Claudication Questionnaire [21] a disease specific quality of life measure.

Illness beliefs will be measured using the Brief Illness Perception Questionnaire [24], adapted to reflect Peripheral Arterial Disease as the illness in question.

There is no standard measure of treatment representations, however walking personal control (walking confidence) questions will be tailored to people with intermittent claudication based on methods described in Francis et al [25]; and treatment consequences (walking) questions will be tailored to people with intermittent claudication based on methods described in Renner & Schwarzer [26].

We will also document all surgery received since the last visit.

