### Evaluation

The effectiveness of the intervention will be determined through analysis of the outcome variables listed above. Analysis of the primary outcome variable will determine whether the brief psychological intervention group have increased walking in comparison with the control group. The psychological measures will be analysed to determine whether improvement in walking is mediated by changes in illness and walking beliefs.

On completion of the study, participants in the intervention group will be asked additional semi-structured questions about their experience of the intervention including what they thought of their action plan, whether they followed their action plan, whether the barriers they predicted prevented them from following their action plan, whether they used their coping plan, whether they intend to follow their action plan in the future, and whether they thought it was worthwhile to take part in the study.

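### The researcher who teaches the target beliefs also administers every questionnaire, so self-report answers may shift toward the expected ones more in the intervention arm

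*Protocol article*

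**What the plan says.** The article describes a single researcher throughout. Under Design she allocates participants, so she knows every allocation. Blinding is stated there only for the Vascular Assessment Nurse and other clinical staff.

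Under Intervention, in Session 1, "The researcher will elicit any maladaptive beliefs the participant has about their illness, or about walking", and information is given "in order to modify illness and walking beliefs". In Session 2, "The researcher will work with the participant to draw up an individualised walking action plan". Under Telephone Calls she rings both arms at 6 and 12 weeks. In the intervention arm only, the call also reviews progress on the plan.

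Under Outcome Measures, "Measures will be taken for participants in both arms of the study, at baseline, 4 months, 1 and 2 year follow-ups", and "All questionnaires will be administered by the researcher". Other Measures lists the scales. "Illness beliefs will be measured using the Brief Illness Perception Questionnaire", and there are also walking-confidence and walking-consequence items, a disease-specific quality-of-life questionnaire, self-reported distance to pain and a self-report activity questionnaire.

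Evaluation uses the belief scores to test "whether improvement in walking is mediated by changes in illness and walking beliefs". Recruitment, which contains the sample size paragraph, makes estimation of the secondary effect sizes a further aim, to help plan a larger study.

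The one stated safeguard is under Control: "4 visits to complete questionnaires and a further 4 visits to either drop off or pick up the pedometer", one visit fewer than in the intervention arm, with talk kept off walking so that social contact is roughly matched.

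**The concern.** At follow-up, intervention participants give their views on illness and walking to the person who set out to change those views and who agreed a walking plan with them. Control participants answer to the same person, but she has taught them nothing on the subject. Any wish to give the expected answer is therefore likely to be stronger in one arm. This is response bias at the time of measurement. Concealed allocation and a baseline taken before allocation would not remove it.

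Three uses of the data are exposed:

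- the between-arm effects on the self-report secondary scales;
- the intervention-to-belief step of the mediation objective, which rests entirely on these answers;
- the secondary effect sizes carried into the planning of the next trial.

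The comparison of self-reported activity with the pedometer is also affected, although it offers a partial check, discussed under the objection.

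**Working it through.** **1. The plan's own figure.** Recruitment gives 26 per condition for a 2 group by 2 time mixed ANOVA, effect size 0.2, alpha 0.05, power 80%. For the group-by-time interaction the noncentrality is λ = f²·N·m/(1 − ρ), with 1 and N − 2 degrees of freedom. The article gives no correlation. With ρ = 0.5 assumed, λ = 0.04 × 52 × 2 / 0.5 = 8.32 on 1 and 50 df, and power is 0.807. So 52 in total, 26 per arm, reproduces. With four time points and the same ρ the total is 36, which agrees with the statement that fewer would be needed. This figure concerns the pedometer outcome and is not disputed.

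**2. Numbers at follow-up.** Recruitment expects 60 participants and 6 drop-outs: 60 − 6 = 54, or 27 per arm if split equally.

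**3. Who does what, by arm.**

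| Contact with the researcher | Intervention | Control |
|---|---|---|
| Taught illness and walking beliefs | yes | no |
| Agreed a walking plan with her | yes | no |
| Calls at 6 and 12 weeks | yes, with plan review | yes, without plan review |
| Questionnaire visits | 4 | 4 |
| Total visits | 9 | 8 |

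Visit numbers are nearly balanced. The first two rows and the plan review are not, and the talk on other topics in the control arm does not alter them.

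**4. Illustrative size.** The article gives no figure for the shift, so the range is an assumption. Suppose the true effect on a scale is zero and intervention-arm answers move by b SD. For a two-sample t-test at two-sided 5% with n = 27 per arm, df = 52 and the noncentrality is b·√(n/2) = b × √13.5 = b × 3.674.

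| Assumed shift b | Noncentrality | Chance of a significant difference |
|---|---|---|
| 0 | 0 | 5% |
| 0.2 SD | 0.73 | 11.1% |
| 0.3 SD | 1.10 | 19.1% |
| 0.5 SD | 1.84 | 43.8% |

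The estimated standardised effect is biased by the whole of b, whether or not the test is significant.

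**5. Mediation.** The intervention-to-belief step is biased by the shift directly. The belief-to-walking step has pedometer steps as its outcome. If the shift varies between participants, it adds error to the belief score and tends to weaken that step. One step may be raised and the other lowered, so the sign of the net bias in the indirect effect cannot be fixed from the article.

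**6. Room for another mode of completion.** Control visits come to 4 + 4 = 8 over four time points, two at each, which fits a drop-off and a pick-up. In the intervention arm the non-session visits come to 4 + 3 = 7, one short of two per time point. One drop-off or pick-up presumably falls on a session visit, although the article gives no timetable.

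**The case against.** The design already guards its main result. Background stresses direct measurement of walking over self-report, the primary outcome is pedometer steps, and the activity questionnaire is included as a comparison for the pedometer, so over-reported walking can be checked. Uptake of surgery is not a scale answer. All of this stands, and it limits the point to the self-report scales. The pedometer comparison does not help with beliefs or quality of life, which have no objective counterpart.

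A reader might infer more than the article supports in four ways:

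- **That the primary result is biased by this route.** It is not; steps are not questionnaire answers.
- **That the mediated effect is inflated.** Only the intervention-to-belief step can be called that, for the reason in step 5 of the working.
- **That controls are under no pressure at all.** Under Usual Care the nurse advises every patient to walk, and the same researcher visits and telephones controls. Some expected-answer pressure is common to both arms and cancels in the comparison. What remains is the increment tied to the teaching and the plan.
- **That the questions are read out face to face.** Administration may already mean that the participant fills in a form while the researcher is present. That would lessen the pressure without removing it.

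It is also fair to say that the range of shifts is wholly assumed, and that the article says only that secondary effect sizes will help to inform the next sample size, not that the next trial will be powered on a self-report scale. Both points stand. They bear on how large the problem is, not on whether the two arms are questioned under different conditions.

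**Conclusion.** The point holds in a limited form. One unblinded researcher teaches the target beliefs in one arm and then administers every scale that measures them, and the stated safeguard balances social contact only. The self-report secondary effects, the intervention-to-belief step, and the secondary effect sizes carried forward may be biased toward the intervention.

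The size is unknown from the document. Under the assumptions of a 0.2 to 0.5 SD shift confined to the intervention arm, no true effect and 27 per arm, the chance of a significant result is about 11% to 44% per scale. Pressure common to both arms, or forms already filled in by the participant, would place the real shift lower than it would otherwise be. The primary outcome and uptake of surgery are untouched by this route. It is an ordinary weakness of a single-researcher pilot, worth correcting because correction is cheap.

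**What to change.** Under Outcome Measures, replace researcher administration with self-completion by participants in both arms at all four time points. Baseline must be included, so that the mode does not change within the repeated-measures analysis.

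- Leave the form at the pedometer drop-off, have it completed without the researcher present, and collect it sealed at pick-up, unopened during the visit.
- At baseline in the intervention arm, have the form completed and sealed before Session 1 begins.
- Limit help to reading or writing, and record when it was given.
- Treat the quality-of-life, pain and walking-distance items from the telephone calls as descriptive only, since the same researcher asks them.
- State the remaining unblinded self-report as a limitation wherever the secondary effect sizes are carried forward.

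Marking envelopes with the participant number alone would not mask allocation, because the researcher assigns those numbers and each corresponds to a group. The gain comes from completion in her absence.

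The cost is envelopes and a change of wording. The existing visits appear sufficient, with no extra staff. Some more items will be missed and some participants will need help. The bias is reduced, not removed, because participants still know what they were taught.

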### Primary Outcome - walking

Previous studies of walking in patients with intermittent claudication have tended to measure maximal walking distance on the treadmill. While this measure gives an accurate idea of how far a patient can walk before they experience claudication pain, and before they have to stop, it does not give any idea of how much walking the patient does in their day to day life, and therefore lacks ecological validity. For this reason, we have decided to measure day-to-day walking using pedometers. Participants will be asked to wear a pedometer for one week at each time point, and their mean daily steps will be calculated by averaging the six days with the highest number of steps.

Patients will be shown how to use the pedometer at each time point, and will be encouraged to telephone the researcher if they have any problems with the pedometer.

### Other Measures

Self-reported walking ability will be measured with the question 'How far can you walk, aided or unaided, under normal circumstances before the onset of pain?' to which there are 6 possible responses - '0 yards', 'up to 100 yards', 'up to 250 yards', 'up to half a mile', 'up to 1 mile', 'more than a mile'. The question is adapted from Mondillo et al's [22] Claudication Self-Assessment with the distances being re-formatted from metres to yards to reflect the fact that older patients are more likely to be confident measuring distance in imperial units. In order to measure frequency of walking to the onset of pain, participants are asked 'In general, how frequently do you walk that distance?' with 6 possible responses - 'never', 'once or twice a month', 'once a week', '2-3 times a week', '4-5 times a week', and 'everyday'.

A self-report measure of walking will also be completed, as a comparison for walking as measured by pedometer. The International Physical Activity Questionnaire (IPAQ) [23] is a self-report measure of physical activity with 4 items measuring time spent in vigorous and moderate activity, time spent walking, and time spent sitting.

Quality of life will be measured using the Intermittent Claudication Questionnaire [21] a disease specific quality of life measure.

Illness beliefs will be measured using the Brief Illness Perception Questionnaire [24], adapted to reflect Peripheral Arterial Disease as the illness in question.

There is no standard measure of treatment representations, however walking personal control (walking confidence) questions will be tailored to people with intermittent claudication based on methods described in Francis et al [25]; and treatment consequences (walking) questions will be tailored to people with intermittent claudication based on methods described in Renner & Schwarzer [26].

We will also document all surgery received since the last visit.

### Analysis

Data will be analysed using an intention to treat protocol in a repeated measures mixed design (2 groups*2 time points for short-term outcome, and 2 groups*4 time points for long-term outcome). Our aim is to determine the effect size achieved by this pilot to inform the sample size calculation for a larger, multi-centre study. Between-group differences in uptake of surgery will be measured using a chi-square test.

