## Background

Patients with Peripheral Arterial Disease (PAD) have been described as 'a high risk, but neglected, disease population' [1]. The disease is common in older adults, has serious health implications, but is not as intensively treated as other cardiovascular diseases [2]. PAD is caused by atherosclerosis in the leg arteries, which leads to a reduction in blood supply to the lower limbs. The most common symptom of PAD is intermittent claudication (IC), leg pain when walking. The prevalence of PAD increases with age, Fowkes et al [3] found that 4.5% of 55 to 74 years olds had IC in the Edinburgh Artery Study, with prevalence increasing to over 20% of over 75 year olds [4].

Atherosclerotic build-up on the walls of arteries is not confined to one part of the arterial system, therefore a diagnosis of IC is an indicator of atherosclerosis in other parts of the body. Indeed, patients diagnosed with IC are at increased risk of cardiovascular co-morbidity and mortality. Caro et al [5] analysed a large database of patients with PAD and found that 33% of patients with PAD died, mainly from cardiovascular events, within 5 years of diagnosis of IC. A diagnosis of IC can therefore be seen as an important early warning sign of future cardiovascular problems, and should trigger measures to reduce the risk of death and vascular co-morbidity [6].

Many of the risk factors for atherosclerosis are behavioural, and include smoking, lack of physical activity, high cholesterol levels, high blood pressure, diabetes and obesity. Treatment for patients diagnosed with IC includes risk factor modification and surgery. Walking benefits patients with PAD as it reduces blood pressure, improves the lipid profile of the blood, and encourages development of a collateral blood supply [7]. In a Cochrane review of exercise for intermittent claudication, Leng et al [8] found significant improvements in walking distance following exercise therapy, the most effective exercise regimens involving walking to near-maximal pain, three times a week. Leng called for further research to determine the degree of supervision required in an exercise programme, and how long changes in exercise could be expected to last following participation in an exercise programme.

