Currently 200 patients are diagnosed each year in the Forth Valley Intermittent Claudication clinic. A sample size calculation carried out using GPower3 [17], indicates that to carry out a (2) group by (2) time mixed ANOVA to detect a small effect size (0.2) with an alpha of 0.05, and a power of 80%, the trial would require 26 participants in each condition. A small effect size of 0.2 was selected in the sample size calculation based on a previous study of an exercise program for physical activity in patients with IC which measured walking outcomes using pedometers [18]. The sample size calculation was based on the conservative initial (2) time point (baseline to 4 month) mixed ANOVA to increase the likelihood that the study was adequately powered to identify an initiation of walking behaviour change. A (4) time point mixed ANOVA sample size calculation required fewer participants in the study, and therefore the larger, initial (2) time point, more conservative sample size calculation was used. The sample size calculation was based on changes in the primary outcome measure. As this is a pilot study, a further aim is to determine the effect sizes achieved in the secondary outcome measures, to help inform the sample size calculation for a larger, more definitive study. Based on a previous study with patients from this population recruited at outpatient clinic, we estimate that 25% of people may decline to participate in the study. Likely attrition rate from the study for this population is unknown, therefore we have estimated a 10% attrition rate during the trial. We therefore aim to invite 80 patients to participate in the trial, of whom we expect 60 to agree to participate, and a further 6 to drop-out during the course of the trial. Based on typical numbers presenting at the clinic who are diagnosed with claudication, recruitment is estimated to take place at the rate of 2 participants/week.

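### The 2x2 mixed ANOVA is a change-score test that forgoes the precision of baseline adjustment, and the 2x4 interaction does not separate initiation from maintenance of walking

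*Protocol article*

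**What the plan says.** The Analysis section of the protocol article plans the following: "Data will be analysed using an intention to treat protocol in a repeated measures mixed design". The layouts are given as "2 groups*2 time points for short-term outcome, and 2 groups*4 time points for long-term outcome". Measures are taken at baseline, 4 months, 1 year and 2 years (Outcome Measures), so two time points means baseline and 4 months, and four means all visits. No baseline covariate is named.

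The Recruitment section names the method in its sample size calculation, which is made "to carry out a (2) group by (2) time mixed ANOVA" with an effect size of 0.2, alpha 0.05 and power 80%. It concludes that "the trial would require 26 participants in each condition". It adds: "The sample size calculation was based on the conservative initial (2) time point (baseline to 4 month) mixed ANOVA". For the long-term version it says: "A (4) time point mixed ANOVA sample size calculation required fewer participants in the study".

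Two stated aims bear on this. The Framework and Analysis sections want an effect size from the pilot for planning a larger trial. The Background, in its fourth point of difference from earlier studies, says that measuring at three follow-ups will let the trial tell initiation of behaviour change from its maintenance.

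**The concern.** A pilot whose main product is an effect estimate should estimate it as precisely as its data allow. With baseline as a time level, the short-term interaction subtracts the whole baseline value from follow-up. Unless rho is 1, that over-corrects and carries baseline noise into the estimate. Using baseline as a covariate removes only the predictable part.

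The long-term layout has a different weakness. With two groups and four visits, the interaction asks only whether the group difference varies somewhere over the four visits. It gives no estimate at 4 months, 1 year or 2 years. Those visits also differ in kind: the Usual Care section says that about 56% of patients go on to angioplasty or surgery, usually within 6 months, but that none will have been treated by the 4-month visit. One global test therefore mixes a pre-procedure contrast with contrasts at visits after many procedures.

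Finally, a classical mixed ANOVA uses only participants with every visit in its layout unless a missing-data method is added. With follow-up to 2 years, that bears on how the intention-to-treat statement is to be carried out in the 2x4 analysis.

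**Working it through.** **Inputs.** Effect size 0.2 (read as Cohen's f), alpha 0.05, power 80%, 26 per arm, 60 recruited and 6 lost (Recruitment). Rho is not stated; 0.5 is assumed where a single value is needed, and a range is shown.

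**1. The plan's own figure.** For the group-by-time interaction with total N, m time points and k = 2 groups: lambda = f²·N·m/(1−rho), df1 = m−1, df2 = (N−2)(m−1).
- m = 2, N = 52, rho 0.5: lambda = 0.04 × 52 × 2/0.5 = 8.32, df 1 and 50, power 80.7%. N = 50 gives 79.1%. So 52 in total, 26 per arm, is reproduced.
- m = 4: N = 36 gives 80.7%, which agrees with the statement that the four-time-point version needs fewer.
- The between-group main effect would need N = 150, so the stated figure is for the interaction.

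**2. The 2x2 interaction is a change-score t-test.** With two time points, the interaction F equals the squared two-sample t on follow-up minus baseline. A check on simulated data (27 per arm) gave F = 10.591 and t² = 10.591. If the group difference in change is d, each interaction effect is ±d/4. So f = d/(4·SD), and f = 0.2 means d = 0.8 SD.

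**3. Precision given up.** With SD 1 at both visits, the per-person variance is 2(1−rho) for change and 1−rho² for the baseline-adjusted analysis. The ratio is (1−rho²)/[2(1−rho)] = (1+rho)/2. Power is for 0.8 SD with 27 per arm (60 − 6 = 54), two-sided alpha 0.05, with one degree of freedom less for the adjusted analysis.

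| rho | change variance | adjusted variance | ratio | power, change | power, adjusted |
|---|---|---|---|---|---|
| 0.3 | 1.40 | 0.91 | 0.65 | 68.4% | 85.6% |
| 0.5 | 1.00 | 0.75 | 0.75 | 82.2% | 91.5% |
| 0.7 | 0.60 | 0.51 | 0.85 | 96.1% | 98.1% |
| 0.8 | 0.40 | 0.36 | 0.90 | 99.5% | 99.8% |

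At rho 0.5, the adjusted analysis reaches 80% power with 20 per arm (81.2%; 19 gives 79.1%), against 26 for change. Put differently, 54 participants analysed with adjustment are worth about 54/0.75 = 72 analysed by change.

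**4. What the 2x4 interaction can see.** Take N = 54, rho 0.5 between all pairs of visits, and group differences in SD units at baseline, 4 months, 1 year and 2 years.
- Effect that vanishes after 4 months, (0, 0.8, 0, 0): mean 0.2, sum of squared deviations 0.64 − 4 × 0.04 = 0.48.
- Effect fully maintained, (0, 0.8, 0.8, 0.8): mean 0.6, sum of squared deviations 1.92 − 4 × 0.36 = 0.48.
- In both cases lambda = (54/4) × 0.48/0.5 = 12.96 on 3 and 156 df, and power is 86.0%.

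The test responds identically to initiation without maintenance and to initiation with full maintenance.

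**5. Complete rows.** At the plan's 10% overall attrition, 54 of 60 have all visits if nobody else misses one. If instead 10% missed each of the three follow-ups independently (an assumption), 60 × 0.9³ = 43.7, about 44, would have all four measurements. The 2x4 interaction at f = 0.2 would still have 88.8% power with 44 and 94.6% with 54. The issue is who contributes to the long-term estimate, not a shortage of power.

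**The case against.** The change-score test is unbiased under randomisation, because regression to the mean acts on both arms equally in expectation. The trial was sized for this test, and the 54 expected to remain exceed the 52 required. So the planned power is met at the assumed rho, and the gain shrinks as rho rises: 15% of variance at 0.7, 10% at 0.8. All of this stands. The first part of the point is lost efficiency, not an error.

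A reader might infer that the plan drops anyone with a missed visit and so contradicts its own intention-to-treat statement. The article does not support that. No sentence excludes such participants, and the term mixed ANOVA appears only in the sample size paragraph. Imputation or a likelihood-based model could satisfy intention to treat, and an article may leave that choice to a fuller document. A participant lost by year 2 also still counts at 4 months, because the short-term analysis is separate.

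A reader might also use the Background figure that "33% of patients with PAD died, mainly from cardiovascular events, within 5 years of diagnosis of IC" to predict losses by 2 years. It comes from a database of patients with PAD, would need a constant-hazard assumption, and takes no account of this trial's exclusions. No analysis recovers steps from participants who have died.

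Nor does the pair of analyses amount to two chances to claim success. They are labelled short-term and long-term, the sample size is tied to the 4-month change, and the stated aim is an effect size. What the objection does not answer is the 3-df interaction, which leaves a stated purpose without a matching estimate.

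**Conclusion.** The point holds as an avoidable loss of precision together with a long-term test that does not match its question. The identity between the 2x2 interaction and the change-score test is exact. The variance ratio (1+rho)/2 assumes equal variances at the two visits and a linear relation. Because rho is not given, the saving is a range: 35% of variance at rho 0.3, 25% at 0.5, 15% at 0.7 and 10% at 0.8. The value 0.5 is the one at which the plan's own 26 per arm reproduces with f = 0.2. There, power with 27 per arm goes from 82.2% to 91.5%.

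The equal 86.0% power for a vanishing and a maintained effect assumes 54 participants, rho 0.5 and equal correlation between visits. The more general fact, that the interaction yields no visit-specific estimate, needs no such assumption.

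On missing visits, the supportable statement is conditional: a classical mixed ANOVA cannot include every randomised participant without an added missing-data method. This is worth correcting before analysis, but it does not make the planned analysis invalid.

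**What to change.** Replace both ANOVAs with one likelihood-based repeated-measures model for mean daily steps at 4 months, 1 year and 2 years. Include baseline steps as a covariate with a separate coefficient at each visit, terms for group, visit and group by visit, and an unstructured covariance (three visits, so six parameters). Use all available follow-up visits of all randomised participants, and report by arm how many have none.

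Report the adjusted 4-month difference with its 95% confidence interval as primary, which matches the sample size basis. Report the 1-year and 2-year differences with intervals as secondary; these address maintenance directly. Also report the observed baseline-to-follow-up correlations, since the larger trial will need them for its sample size.

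The cost is a change of wording in the Analysis section. Baseline steps are already collected, and no visit, measurement or participant is added. The sample size can stay as it is.
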